## Objectives

In sum, the treatment of AiWG is currently very challenging and few interventions have been investigated in well powered trials of sufficient quality. Therefore, this randomized, double blind, multicenter, placebo-controlled, pragmatic trial aims to evaluate the effect of metformin doses up to 2000 mg daily for AiWG as an additional strategy next to treatment as usual including lifestyle interventions, by comparing metformine plus the lifestyle intervention with placebo plus the lifestyle intervention. In the event of a significantly greater reduction of AiWG following metformin use in combination with care as usual including a lifestyle intervention, guidelines can include metformin for AiWG. Furthermore, we aim to investigate the difference in metformin-associated reduction of AiWG between participants using clozapine versus other antipsychotics; between participants on high-AiWG risk agents (i.e. olanzapine, clozapine, quetiapine, risperidone and paliperidone) compared to all other antipsychotics; and the difference between self-reported weight gain due to antipsychotic use versus weight gain due to other reasons [2, 12]. At last, we aim to examine whether lifestyle interventions in combination with metformin or placebo improve metabolic traits, quality of life, general physical and psychological health, cost effectiveness, and whether genetic liability to BMI and MetS allows adequate estimation of weight reduction following initiation of metformin and lifestyle interventions.

Metformin and placebo both combined with treatment as usual including lifestyle interventions are the conditions we wish to evaluate with difference in body weight as the primary outcome measure. We hypothesize that metformin given adjunctively to lifestyle interventions will lead to a higher level of weight reduction and better quality of life, compared to placebo in combination with lifestyle interventions.

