### Randomization and blinding

After eligibility screening and providing written informed consent, participants will be randomized using block-randomization with a 1:1 allocation to 1) placebo; or 2) metformin. Randomization will be stratified for clozapine use versus other antipsychotic use additional to stratification for participating sites using a computer-generated double-blind application developed by the UMC Utrecht’s Data Management department. The block sizes will not be disclosed. Allocation concealment will be facilitated by releasing the randomization code only after the participant has completed all baseline assessments and has been included in the trial.

The participant, caregiver, investigator and outcome assessor will be blind to treatment allocation. Placebo tablets will be matched to metformin tablets in size and appearance. Unblinding for all participating sites will be performed by the study sponsor whenever needed for safety reasons. For this purpose, a set of sealed envelopes comprising the information on the type of medication stored in every medication box used in the trial will be sent to the UMC Utrecht pharmacy. This pharmacy will provide a 24/7 backup emergency unblinding service. Participants will be excluded from subsequent statistical analyses after unblinding of the treatment allocation.

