### Statistical analysis

#### Sample size calculation

A regression of weight on treatment with a sample size of 128 observations achieves 80% power at a two-sided 0.05 significance level to detect a difference in a weight reduction of two kgs (SD = 4, ES = 0.5) after 26 weeks (PASS 2008, version 8.0.16). We estimate the drop-out rate to be a maximum of 50% as such attrition rates are most commonly reported in trials targeting schizophrenia patients [37]. Drop-outs are those not attending the visit at 26 weeks. As soon as 128 subjects have completed this visit, inclusion will be stopped. Considering the estimated drop-out rate, we will therefore include approximately 256 subjects to ensure that 128 subjects complete the visit at 26 weeks. This power calculation is based on an independent two-sample t-tests of the outcome at 26 weeks. Using linear models in the data analysis will increase the efficiency of the analysis and therefore the power to detect a treatment effect.

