#### Data analysis

The primary analysis in this trial tests the effect of metformin use next to care as usual including lifestyle interventions on body weight with a primary comparison at 26 weeks after treatment onset. This will be analyzed using a general linear mixed model with treatment group, baseline weight, gender, age, timepoint (as categorical factor) and compliance with lifestyle therapy as fixed factors and patient as random factors. Measurements of visit 3 (week 13) and visit 4 (week 26) will be included in the primary analysis models. Missing baseline parameters will be imputed before the analyses, but mixed models can handle missing outcome variables at post-randomization weeks if these are missing at random (MAR). The pattern of missingness will be examined. As a sensitivity analysis, body weight at 26 weeks will also be analyzed using an ANCOVA with treatment group and gender as factors and baseline weight and age as covariates. The significance threshold is set at *p* < 0.05. Considering the study population, we expect a high number of dropouts [37]. Additionally, we expect participants within one stratification group may switch clozapine or other antipsychotic use. Taking into account the pragmatic design of this study, the Intention-To-Treat principle will be followed for the primary and secondary analyses. In secondary analysis, the effect of metformin on body weight after 26 weeks of treatment will be compared to body weight at 52 weeks after 26 weeks of non-treatment with metformin. In this way, we can examine whether the possible effect of metformin on AiWG continues after 26 weeks of non-treatment following discontinuation of metformin use after 26 weeks of treatment. In a sensitivity analysis, per-protocol analysis will be applied for all analyses. Non-adherent participants to study medication defined as less than 80% of pills being taken will be excluded (see ‘Trial design’) [42, 43].

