Similar analyses to the abovementioned primary study parameter analyses will be applied to the secondary outcomes, using generalized linear mixed models with appropriate link functions where necessary. For exploratory purposes, the following subgroup analyses within subtypes of patients will be conducted using the same model to explore possible differences in treatment effects: those on clozapine vs. those on other antipsychotics and those on high-risk agents (olanzapine, clozapine and quetiapine, risperidone and paliperidone) vs. all other antipsychotics [2, 12]. In post-hoc sensitivity analysis, the quantitative measure of the amount of self-reported AiWG will be used to examine differences between AiWG and weight gain due to other reasons.

For genetic analyses, we will run a linear model of polygenic risk scores (PRS) for BMI and MetS to assess their association with weight reduction. Covariates will be age, sex and three principal components of genetic ancestry. At each *p*-value threshold going from 5 × 10–8 to, 5 × 10–7, 5 × 10–6, 5 × 10–5, 5 × 10–4, 5 × 10–3, 0.01, 0.05, 0.1, 0.2, 0.3, and 0.4 both the variance in BMI/MetS and the p-value of the association will be computed to visualize the strength of association and degree of explained variance per p-value bin [55]. The optimal p-value threshold will be computed using PRSice (https://www.prsice.info/) or similar methods and reported. The significance threshold is set at *p* < 0.05.

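### The exploratory subgroup analyses fit the model separately within each subgroup, so they do not estimate or test the difference in metformin effect that the Objectives name

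*Protocol article*

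**What the plan says.** In the Objectives section of the protocol article the aim is a contrast between subgroups: "we aim to investigate the difference in metformin-associated reduction of AiWG between participants using clozapine versus other antipsychotics". The same sentence adds the contrast of high-risk agents with all other antipsychotics. Clozapine use is also a design factor, since Randomization and blinding states: "Randomization will be stratified for clozapine use versus other antipsychotic use additional to stratification for participating sites".

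The method is in Data analysis. Under an explicit exploratory label, "the following subgroup analyses within subtypes of patients will be conducted using the same model to explore possible differences in treatment effects", and the two contrasts are then listed. The model meant is the primary one: treatment group, baseline weight, gender, age, categorical timepoint and compliance with lifestyle therapy as fixed effects, and patient as a random effect. No subgroup term and no treatment-by-subgroup term is named there or elsewhere in the article.

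The third contrast in the Objectives, self-reported antipsychotic-induced gain versus gain for other reasons, is handled separately through a quantitative measure.

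**The concern.** A question about a difference between two treatment effects is answered by estimating that difference. The stated method estimates each effect by itself. Followed literally, it leaves the reader to compare two results, and the usual shortcut is to ask which one reached p < 0.05. That comparison is unreliable: with subgroups much smaller than the trial, one can miss significance by chance or through its size alone, even when metformin works equally well in both.

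At stake is a mistaken statement that metformin works in clozapine users but not in others, or the reverse. Such a statement would attract attention, because the Study population section gives a mechanistic reason to expect a difference and randomisation is stratified on clozapine use. The trial's main comparison is not at stake.

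**Working it through.** **Inputs.** All are from Sample size calculation unless marked. It states that "a sample size of 128 observations achieves 80% power at a two-sided 0.05 significance level". The target is a 2 kg difference with an SD of 4 kg, a standardised effect of 0.5. On the basis of the calculation it says: "This power calculation is based on an independent two-sample t-tests of the outcome at 26 weeks". Allocation is 1:1 (Randomization and blinding). The subgroup shares are not given. I assume that the smaller subgroup holds 20% to 50% of the 128 completers. The formulas are symmetric in the share, so the range applies to either contrast, whichever side is smaller.

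**Step 1: the plan's own figure.** Normal approximation: n per arm = 2 × (1.96 + 0.84)² × (4/2)² ≈ 62.8, so 63 per arm and 126 in total. The t-test gives 63.77, so 64 per arm and 128 in total, with power 0.801. With 50% drop-out, 128 / (1 − 0.5) = 256. The stated 128 and 256 reproduce. This power is for the whole trial; no subgroup contrast is powered.

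**Step 2: separate tests, equal true effect of 2 kg.** For share s, the per-arm sizes are n₁ = 64s and n₂ = 64(1 − s). Let p₁ and p₂ be the t-test powers at standardised effect 0.5. The subgroups do not overlap, so

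P(exactly one significant) = p₁(1 − p₂) + p₂(1 − p₁).

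**Step 3: interaction.** SE of the difference in effects = 4 × √(2/n₁ + 2/n₂). The difference detectable with 80% power is (1.96 + 0.84) × SE.

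| Smaller share | Completers | p₁ / p₂ | Exactly one significant | Interaction SE (kg) | Power for a 2 kg difference | Detectable at 80% (kg) |
|---|---|---|---|---|---|---|
| 20% | 26 / 102 | 0.229 / 0.707 | 0.613 | 1.768 | 0.205 | 4.95 |
| 25% | 32 / 96 | 0.278 / 0.679 | 0.579 | 1.633 | 0.232 | 4.57 |
| 30% | 38 / 90 | 0.326 / 0.648 | 0.552 | 1.543 | 0.254 | 4.32 |
| 40% | 51 / 77 | 0.418 / 0.580 | 0.513 | 1.443 | 0.283 | 4.04 |
| 50% | 64 / 64 | 0.504 / 0.504 | 0.500 | 1.414 | 0.293 | 3.96 |

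Example at 20%: n₁ = 12.8 and n₂ = 51.2, so SE = 4 × √(0.156 + 0.039) = 1.77 kg.

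**Step 4: no effect in either subgroup.** P(exactly one significant) = 2 × 0.05 × 0.95 = 0.095.

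**Step 5: the comparator.** An interaction test at the 5% level falsely signals a difference in 5% of trials, whether the common effect is 2 kg or zero.

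**Step 6: sensitivity to the SD.** Covariate adjustment may reduce the residual SD. At an assumed 3.2 kg (standardised effect 0.625), step 2 gives 0.63 at a 20% share and 0.43 at 50%. The size of the problem does not rest on the unadjusted SD.

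**The case against.** The strongest reply has three parts.

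- **The analyses are exploratory.** This is true and limits the weight of the point. But the label does not make two separate p-values answer a question about their difference, and the Objectives list that difference as an aim.
- **The sentence speaks of differences in treatment effects and sets one group against the other, so a contrast may be intended.** There is some room for this. Two estimates from non-overlapping groups, with their standard errors, would also let the difference and its interval be calculated afterwards. But the article names the method, separate fits of the same model, and does not name that further step. An SAP could supply it; the stated method does not.
- **The interaction test is weak here.** It is: power for a 2 kg difference is 21% to 29%, and about 503 (50/50) to 785 (20/80) completers would be needed for 80%. Neither method can settle the question at this size. A wide interval shows that openly, and two p-values conceal it.

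A reader might go further in four ways that the documents do not support.

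- **That subgroups will be formed by current drug, and so after randomisation.** The plan says "we expect participants within one stratification group may switch clozapine or other antipsychotic use", but then applies the intention-to-treat principle, and clozapine use is a stratum fixed at randomisation. No text groups by current drug.
- **That discordant results are frequent whatever the truth.** The 50% to 61% figure needs a real, equal effect; without any effect it is 9.5%.
- **That guideline conclusions are undermined.** The Objectives tie these to the overall comparison.
- **That the self-reported weight-gain analysis has the same fault.** It uses a quantitative measure under a separate sentence, and no such fault is shown.

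**Conclusion.** The point stands for two exploratory contrasts: clozapine versus other antipsychotics, and high-risk versus other agents. The stated method does not deliver the quantity that the Objectives name.

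The size is conditional. It assumes that each subgroup is judged by its own p-value, that the true effect is 2 kg in both, that 128 participants complete, and that the unstated subgroup share lies between 20% and 50%. It also uses a week-26 t-test, whereas the planned model adds week 13 and covariates. Under these assumptions a false contrast between the subgroups is about 10 to 12 times as likely as with an interaction test (0.50/0.05 to 0.613/0.05). With no effect in either subgroup the ratio is about 1.9 (0.095/0.05).

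This is worth correcting but moderate in weight.

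**What to change.** For these two contrasts, replace the separate fits with one model in all randomised participants that includes subgroup and a treatment-by-subgroup term evaluated at week 26. Take subgroup from the antipsychotic at randomisation; for clozapine, this is the randomisation stratum. Report the difference in effect with its 95% CI as the subgroup result, and show the within-group estimates for description only. Keep the exploratory label, and add that a non-significant interaction does not show that the effects are equal.

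The cost is a sentence or two of text, with no new data, no change in sample size and no change to the primary analysis. The downside is a wide interval: with an SE of 1.4 to 1.8 kg, the 95% CI extends roughly 2.8 to 3.5 kg either side of the estimate (1.96 × 1.414 to 1.96 × 1.768).

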**Methods:**

In this randomized, double-blind, multicenter, placebo-controlled, pragmatic trial with a follow-up of 52 weeks, we aim to include 256 overweight participants (Body Mass Index (BMI) > 25 kg/m^2^) of at least 16 years of age. Patients are eligible if they have been diagnosed with schizophrenia spectrum disorder and if they have been using an antipsychotic for at least three months. Participants will be randomized with a 1:1 allocation to placebo or metformin, and will be treated for a total of 26 weeks. Metformin will be started at 500 mg b.i.d. and escalated to 1000 mg b.i.d. 2 weeks thereafter (up to a maximum of 2000 mg daily). In addition, all participants will undergo a lifestyle intervention as part of the usual treatment consisting of a combination of an exercise program and dietary consultations. The primary outcome measure is difference in body weight as a continuous trait between the two arms from treatment inception until 26 weeks of treatment, compared to baseline. Secondary outcome measures include: 1) Any element of metabolic syndrome (MetS); 2) Response, defined as ≥5% body weight loss at 26 weeks relative to treatment inception; 3) Quality of life; 4) General mental and physical health; and 5) Cost-effectiveness. Finally, we aim to assess whether genetic liability to BMI and MetS may help estimate the amount of weight reduction following initiation of metformin treatment.

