## Discussion

Here, we describe the design of a pragmatic, randomized, double blind, multicenter controlled clinical trial to investigate whether metformin up to 2000 mg daily for 26 weeks in combination with treatment as usual including lifestyle interventions reduces AiWG in comparison to placebo in combination with lifestyle interventions.

The current trial has the following added value over earlier published trials regarding [29]. First, in line with clinical practice, where many patients treated with a range of antipsychotics report AiWG, inclusion is not restricted to certain antipsychotics, thus allowing us to evaluate whether this combination treatment is effective in the entire group of antipsychotics users. Second, the inclusion criteria are less strict than in previous trials, thus ensuring that the study population reflects clinical practice where some patients are not given a diagnosis of schizophrenia (but of another psychotic disorder) and may experience weight gain as problematic even if this is less than 10% (weight gain > 10% was an inclusion criterion in the Chinese 2008 trial) [28]. Third, the intervention is more feasible. The exercise program for participants in the current trial is less intense than other exercise programs: for example, our exercise program consists of two sessions weekly as opposed to seven in the published trial [28]. We expect that this increases feasibility and thus the likelihood of implementation in this patient group. Fourth, this is the first clinical trial examining the use of metformin in addition to lifestyle therapy for the treatment of AiWG in residents of a North-Western European country. This is relevant as cultural and genetic vulnerability factors may influence treatment adherence and efficacy. Fifth, we treat patients for 26 weeks as opposed to 12 weeks in the published trial, thus allowing us to better ascertain drop-outs and temporal patterns in treatment response [28]. At last, as it is currently impossible to predict who will benefit from treatment of AiWG with metformin we also include genetic analyses to assess whether polygenic risk scores are associated with metformin treatment response.

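### The polygenic-score model has no treatment term, so it cannot show who responds to metformin, and picking the best of 12 thresholds for two scores at an unadjusted 0.05 inflates false positives several-fold

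*Protocol article*

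**What the plan says.** The aim appears in three places in the Protocol article. The Abstract (Methods) asks "whether genetic liability to BMI and MetS may help estimate the amount of weight reduction following initiation of metformin treatment". The Objectives section words it more loosely, as estimating weight loss after starting metformin together with the lifestyle intervention. The Discussion notes that nobody can yet predict who will benefit from metformin, and says the genetic analyses are included "to assess whether polygenic risk scores are associated with metformin treatment response".

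The method is under Data analysis: "we will run a linear model of polygenic risk scores (PRS) for BMI and MetS to assess their association with weight reduction". The adjustment set is listed: "Covariates will be age, sex and three principal components of genetic ancestry". The score is evaluated at a series of p-value thresholds from 5 × 10⁻⁸ upward, ending in "0.01, 0.05, 0.1, 0.2, 0.3, and 0.4". At each one, "both the variance in BMI/MetS and the p-value of the association will be computed". Then "The optimal p-value threshold will be computed using PRSice" or a similar method, and the result is reported. The paragraph closes by setting significance at p<0.05. It mentions no permutation, multiplicity correction or hold-out sample.

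**The concern.** There are two substantive problems and one slip of wording.

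1. **The model does not match the aim.** Who benefits from metformin is a question of effect modification: does the difference between metformin and placebo vary with the score? A model without arm and score-by-arm estimates only how the score relates to weight change averaged over everyone, about half of whom take placebo under the 1:1 allocation.

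2. **Selection is not accounted for.** The threshold with the strongest association is chosen on the same data that test it, for two scores, and is still judged at 0.05.

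3. **Explained variance is attached to the wrong variable.** The text names BMI/MetS, whereas the outcome of the model is weight reduction.

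A chance finding, or a purely prognostic association, could then be published as genetic prediction of metformin benefit.

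**Working it through.** **Inputs from the Protocol article.** 128 completers, a difference of 2 kg, SD 4 and two-sided 0.05 (Sample size calculation); 1:1 allocation (Randomization and blinding); two scores, the covariate list, the thresholds and p<0.05 (Data analysis).

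**The plan's own figure.** With 64 per arm, a 2 kg difference and SD 4, power is 80.1% by the noncentral t distribution, and 128/(1 − 0.5) = 256. The main sample size reproduces. The only figure stated for the genetic analysis is its 0.05 threshold.

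**Step 1: what the missing treatment term does.** Take n = 128, a 2 kg arm effect and a residual SD of 4. The score effects below are illustrative assumptions, per SD of the score.

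- Pooled model: leaving out arm adds 2² × 0.25 = 1 to the residual variance, so SE = √(17/128) = 0.364 kg.
- Interaction model: SE = 4 × √(1/64 + 1/64) = 0.707 kg.
- Purely prognostic score, 1 kg in both arms: pooled z = 1/0.364 = 2.74, power about 78%.
- Opposite effects, +1 kg and −1 kg: the pooled slope averages to 0, so the pooled test rejects at about its nominal rate. The interaction z is 2/0.707 = 2.83, power about 81%.
- Effect of 1 kg in the metformin arm only: interaction z = 1/0.707 = 1.41, power about 29%.

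Simulation (4,000 trials per case, without the other covariates) agrees:

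| True situation | Pooled test rejects | Score × arm test rejects |
|---|---|---|
| Prognostic only, no bearing on metformin effect | 77% | 5% |
| Opposite direction by arm | 6% | 79% |
| Effect in metformin arm only | 27% | 29% |

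**Step 2: the number of tests.** The thresholds are 5 × 10⁻⁸, 5 × 10⁻⁷, 5 × 10⁻⁶, 5 × 10⁻⁵, 5 × 10⁻⁴, 5 × 10⁻³, 0.01, 0.05, 0.1, 0.2, 0.3 and 0.4. That is 12, so two scores give 24 tests. If the tests were independent, the chance of at least one p<0.05 under the null would be 1 − 0.95¹² = 46.0% for one score and 1 − 0.95²⁴ = 70.8% for two. These are upper bounds, because the scores overlap. Two scores at one fixed threshold each would give 1 − 0.95² = 9.75%.

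**Step 3: allowing for correlation.** The rate is P(max|z| > 1.96) over 12 z-scores whose correlation decays as r to the power of their distance, from 200,000 null draws. The document gives no correlations, so both r and the between-score correlation (0 to 0.8) are assumed.

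| Adjacent r | One score | Two scores |
|---|---|---|
| 0.6 | 38% | 53–62% |
| 0.8 | 29% | 41–50% |
| 0.9 | 21% | 31–38% |
| 0.95 | 16% | 23–29% |
| 0.99 | 9% | 14–18% |

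**Step 4: a check on plausible correlations.** Nested scores built from independent variants, weighted by effect size under five assumed genetic architectures, give 13–22% for one score and 24–39% for two. With equal weights, the correlation between two nested sets of m₁ < m₂ variants is √(m₁/m₂), for example √(3120/7533) = 0.64. Depending on the set sizes, the rates are then about 23–33% for one score and 41–55% for two (uncorrelated scores).

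**Step 5: the nominal p needed to hold 5% over the two-score scan.** It is 0.05/24 = 0.0021 if independent. For uncorrelated scores it is 0.0043 at r = 0.9, 0.0063 at r = 0.95 and about 0.012 at r = 0.99.

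**The case against.** **The aim may be prognostic.** The Abstract and Objectives speak of estimating weight reduction, which need not require an interaction. The analysis population is not stated either, and a model fitted only in the metformin arm would have no arm term. This stands in part: a pooled model partly serves the Objectives wording. It does not serve the Discussion, and restricting to the metformin arm is nowhere stated. Even if it were done, it would not separate response to metformin from weight change that would have occurred anyway.

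**Correction may be left to the SAP or to software settings.** The per-threshold p-values are for display, "the p-value of the association will be computed to visualize the strength of association", and the text does not say whether the p-value compared with 0.05 is raw or empirical. That is true. But the article itself fixes the scan, the data-driven optimum and a flat 0.05, and names no setting that corrects for selection.

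**The upper rates may be too high.** Scores at neighbouring thresholds share many variants, and BMI and MetS scores may be correlated. The 62% is indeed the unfavourable end: r = 0.6 throughout and uncorrelated scores. For one score with near-identical thresholds, inflation falls to about 1.8 times. But the equal-weight checks reach 55% for two scores, so high values cannot be dismissed, and the two-score rate is well above 5% in every case tried.

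**The analysis is ancillary.** It is not among the listed outcomes, DNA sampling is optional, and no sample size rests on it. This stands and limits the severity. Yet the exploratory label in Data analysis is attached to the antipsychotic subgroups, while the genetic analysis carries its own significance threshold.

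**The variance wording is a slip.** Agreed; it needs only an editorial correction.

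**Conclusion.** The concern holds. As written, the model cannot separate a prognostic score from one that modifies the metformin effect, so it does not answer the question posed in the Discussion. This follows from the listed covariates and needs no assumption; the rejection rates that illustrate it rest on assumed effects of 1 kg per SD.

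For the threshold selection, the false-positive rate is 38% down to 16% for one score and about 62% down to 23% for two, for adjacent correlations of 0.6 to 0.95. Extending the correlation to 0.99 lowers these to 9% and 14–18%. The two-score rate is therefore about 3 to 12 times the nominal 5% across these cases. The exact multiple depends on correlations the document does not give.

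The point should be corrected, but it concerns a secondary genetic aim. The primary comparison and its sample size are untouched.

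**What to change.** - Fit weight change on score, treatment arm and score × arm, adjusting for baseline weight, age, sex and the ancestry components. Name the score × arm interaction as the test of metformin response, and report the score's association with weight change as prognostic. Baseline weight is a modelling choice, consistent with the primary model; the arm and interaction terms are what the aim requires.
- Either pre-specify one threshold per score and test each at 0.025, or keep the 12-threshold scan and report a permutation p-value that repeats the selection in each permutation, corrected for two scores.
- Report explained variance in weight change.
- Align the wording of the aim across the Abstract, Objectives and Discussion.

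The cost is wording and a permutation run. Reported p-values become less favourable. The interaction test has low power, about 29% for a 1 kg per SD effect confined to the metformin arm with 128 genotyped completers, and less if fewer give DNA. The protocol should say so.
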